### Recruitment

Parents will be recruited through social media, posters, and in-person outreach (eg, clinics and the family newborn unit). Social media advertisements will be used to recruit parents who are more than 28 weeks pregnant or within 7 days post partum; in addition, parents will be recruited on the birth unit and the family newborn unit at IWK Health, where print posters will be displayed in the patient rooms. Additional outreach strategies may include promotion through public health services, family resource centers, media campaigns, other hospitals across Nova Scotia, and word of mouth. A research team member may also approach families at relevant clinics or units at IWK Health if a nurse within their circle of care has received approval from the family to be approached for research. Participants who contact us by texting “pregnant” to the study mobile phone number when they are less than 28 weeks pregnant will be sent a follow-up message once they reach 28 weeks, until the required sample size is achieved.

### Screening and Baseline

Interested participants will complete a standardized SMS text message script for the eligibility screening process. During prenatal screening, participants will be assessed for preliminary eligibility, and those who qualify will be asked to text the study mobile phone number within 7 days of giving birth to be enrolled. At this stage, participants will be encouraged to provide their partner’s mobile phone number, if applicable, so that the partner’s interest can be assessed. Once a birthing person gives birth or enrolls post partum, they will complete additional screening questions to confirm eligibility.

After the birth of their child, all interested participants will complete the postpartum eligibility and randomization processes. During this stage, additional information will be collected, including the newborn’s name, date of birth, and feeding preference (ie, breast or chest feeding, formula feeding, or combination feeding). Participants will then be randomly assigned to the intervention or control group and asked to complete the consent form and baseline survey. If a parent dyad is participating, the nonbirthing partner will be sent an SMS text message after randomization to indicate their preferred type of feeding messages and to complete the consent form and baseline survey. Linked parent dyads will always be placed in the same intervention group. If dyad members complete the screening process separately and are inadvertently assigned to different groups, both parents will be moved to the intervention group.

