### Eligibility Criteria

Participants will be recruited prenatally and postnatally. To pre-enroll prenatally, eligible birthing parents will (1) be pregnant (>28 wk) with their first child, (2) understand English, (3) have a mobile phone with SMS text messaging functionality and a data plan, and (4) live in Nova Scotia. Eligible nonbirthing parents will (1) have a pregnant (>28 wk) partner (ie, the birthing parent) expecting their first child or will be expecting their first child via an alternative method (eg, adoption or surrogacy), (2) understand English, (3) have a mobile phone with SMS text messaging functionality and a data plan, and (4) live in Nova Scotia. Participants who pre-enroll prenatally will only be considered enrolled and assigned a study number once they text “birth” to the study mobile phone number and are randomly assigned.

To enroll postnatally, eligible birthing parents will (1) be early postpartum (<7 d) with their first child, (2) understand English, (3) have a mobile phone with SMS text messaging functionality and a data plan, and (4) live in Nova Scotia. Eligible nonbirthing parents will (1) be early postpartum (<7 d) with their first child, (2) understand English, (3) have a mobile phone with SMS text messaging functionality and a data plan, and (4) live in Nova Scotia.

Participants (both birthing and nonbirthing parents) will be excluded if they (1) have a newborn who dies or is expected to die before leaving the hospital; (2) have no access to a mobile phone, either personal or shared; (3) are unwilling to receive SMS text messages; (4) decline participation or withdraw; or (5) participated in a previous iteration of this project (eg, development or evaluation). Parents are not required to participate as dyads to be inclusive of all family compositions; however, involvement of the other parent, if applicable, will be encouraged. Participants who do not fully complete the baseline survey will be considered withdrawn from the study. If the participant was randomly assigned to the intervention, they will continue to receive the messages, but no further data will be collected from them.

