### Blinding

Due to the complex nature of Essential Coaching Postpartum, participants cannot be blinded and will be informed of their group allocation. To minimize blinding of personnel in relation to data collection, no hospital staff (eg, nurse midwives, physicians, and other health care providers) will be aware of participant involvement in the study. This is feasible because Essential Coaching Postpartum is delivered directly to participants’ personal mobile phones, with no in-person intervention. The research team will be aware of participant allocation and will track data collection but will not be involved in the randomization process, which occurs automatically through the TextIt platform. As all study procedures are conducted remotely through a preconfigured system, the research team has no direct interaction with participants, thereby reducing any risk of influencing participant responses.

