### Intervention Group

Participants will receive the standard education provided at the hospital where they give birth. After enrollment, participants in the intervention group will receive messages until 6 weeks post partum. Birthing parents will receive Essential Coaching for Every Mother, and nonbirthing parents will receive Essential Coaching for Every Partner. Figure 1 provides examples of messages from each program. Messages are automatically scheduled according to the infant’s date of birth, beginning on the second evening after birth. Participants who enroll later will receive messages starting from their enrollment date (eg, someone who enrolls on day 5 will not receive messages from days 2-4). TextIt will be used to program and schedule the messages, and Twilio (Twilio Inc) [39] will serve as the secure gateway for sending and receiving messages. Participants are not restricted from seeking additional postpartum support outside of the study. They will continue to have access to standard perinatal care, including mental health services available through primary care providers and community resources.

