### Data Analysis

Data will be analyzed on an intention-to-treat basis. Demographic characteristics, including parental age, marital status, educational level, and delivery method (eg, vaginal or cesarean), will be summarized using means and SDs or percentages, as applicable. Postnatal health care contacts for the parent and infant, health concerns, and feeding behavior will also be reported using means and SDs or percentages, as applicable. Any significant differences in baseline characteristics, assessed using chi-square tests or Mann-Whitney *U* tests, will be adjusted for in subsequent analyses. A *P* value of <.05 will be considered statistically significant for all outcomes.

For the primary and secondary outcomes, analysis of covariance will be used to determine whether scores differ between the 2 groups, with adjustments for pretest scores and any significant baseline characteristics. For the exploratory analysis, dyadic actor-partner interdependence multivariate multilevel modeling will be used to examine each dyad member’s relationship to primary and secondary outcomes after accounting for other explanatory variables. For implementation data, quantitative responses will be reported, and thematic analysis [48] will be conducted to describe participants’ experiences with Essential Coaching Postpartum.

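### Consent and the baseline survey follow randomisation and non-completers are dropped, so the analysed set is selected after allocation, contrary to the stated intention-to-treat analysis

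*Protocol article*

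**What the plan says.** All references are to the protocol article.

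- **Order of steps (Screening and Baseline).** After the birth and the eligibility questions: "Participants will then be randomly assigned to the intervention or control group and asked to complete the consent form and baseline survey".
- **Linked dyads (same section).** Once the dyad is allocated, "the nonbirthing partner will be sent an SMS text message after randomization to indicate their preferred type of feeding messages"; that message is also the partner's first request for consent and baseline answers. The same section lets the partner's phone number be given at prenatal screening so that interest can be gauged earlier.
- **Non-completers.** Ethical Considerations counts a parent without a completed consent form or baseline survey as withdrawn. Eligibility Criteria says: "Participants who do not fully complete the baseline survey will be considered withdrawn from the study". It adds that such a parent, if allocated to the intervention, goes on getting messages while data collection stops.
- **Enrolment and messages.** For parents who pre-enrol in pregnancy, Eligibility Criteria counts them as enrolled once they text after the birth "to the study mobile phone number and are randomly assigned". Intervention Group says: "After enrollment, participants in the intervention group will receive messages until 6 weeks post partum".
- **Blinding.** "participants cannot be blinded and will be informed of their group allocation".
- **Data Analysis.** "Data will be analyzed on an intention-to-treat basis". The model is an analysis of covariance adjusted for the pretest score.
- **Sample Size.** 141 evaluable parents of each type, inflated for 15% attrition to 166.

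**The concern.** Randomisation protects a comparison only if the people compared are those who were randomised, or if later losses are unrelated to arm. Here two conditions for being analysed, consent and a completed baseline, are met after the arm is fixed. A parent who fails the baseline condition has no 6-week or 6-month outcome, so no later analysis plan can restore that parent. The same holds for linked nonbirthing partners, whose population carries the primary objective.

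The second issue is the covariate. A baseline score recorded after allocation is not guaranteed to be unaffected by it. If the arm has already moved the score, adjusting for it removes part of the treatment effect.

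A third, conditional issue is size. If the 166 is counted at randomisation, parents lost before completing baseline use up an allowance that may have been meant for later attrition.

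**Working it through.** **1. The passages side by side**

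| Step | What the plan fixes | Section |
|---|---|---|
| 1 | Eligibility questions, then random split | Screening and Baseline |
| 2 | Consent form and baseline survey, after the split | Screening and Baseline |
| 3 | No consent or no baseline means withdrawn | Ethical Considerations; Eligibility Criteria |
| 4 | Incomplete baseline means no further data | Eligibility Criteria |
| 5 | Intention-to-treat, adjusted for pretest score | Data Analysis |

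Steps 1 to 4 give an analysable set of parents who were randomised and consented and completed baseline. Step 5 claims the set of all randomised parents. The two differ whenever anyone fails at step 2.

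**2. The plan's own figure**

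141 / (1 − 0.15) = 165.9, rounded up to 166. This reproduces the target, with no separate allowance for parents lost at step 2.

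The SD is not given. Back-solving from a difference of 4, two-sided 5%, 80% power and 70.5 per arm:

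SD = 4 × √(70.5/2) / (1.960 + 0.842) ≈ 8.48.

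**3. Possible bias (assumed inputs)**

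Let e_I and e_C be the shares excluded in the intervention and control arms, and D the mean outcome of excluded minus retained parents, taken as equal in both arms. The retained mean in an arm is its full mean − e × D, so the bias (intervention minus control) is (e_C − e_I) × D. The documents give none of e_I, e_C or D. Type I error uses 83 per arm and 15% later loss.

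| e_I v e_C | D | Bias (points) | Type I error |
|---|---|---|---|
| 15% v 15% | −0.25 or −0.5 SD | 0 | 5.0% |
| 5% v 15% | −0.25 SD (−2.12) | 0.10 × −2.12 = −0.21 | 5.2% |
| 5% v 15% | −0.5 SD (−4.24) | 0.10 × −4.24 = −0.42 | 5.9% |
| 10% v 30% | −0.25 SD | 0.20 × −2.12 = −0.42 | 5.8% |
| 10% v 30% | −0.5 SD | 0.20 × −4.24 = −0.85 | 8.2% |

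Reversing either the imbalance or the prognosis of excluded parents reverses the sign.

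**4. Power, on one reading only**

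Suppose the 166 is counted at randomisation and the 15% covers only loss after baseline. With an assumed share e lost before baseline is complete, evaluable n = 166 × (1 − e) × 0.85, and power = Φ(4 / (8.48 × √(2/(n/2))) − 1.96).

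| e | n | Power |
|---|---|---|
| 0 | 141 | 80% |
| 10% | 127 | 76% |
| 20% | 113 | 71% |
| 30% | 99 | 65% |

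**The case against.** The strongest defence is that the core conflict may do little harm, and that several stronger readings go beyond the text. A reader might infer the following.

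- **Messages start before consent.** The text implies only that messages can start before baseline is complete: enrolment is tied to randomisation (for prenatal pre-enrollees), messages run from enrolment, and they go on after an incomplete baseline. The rule on continuing messages does not mention parents who never consent, and no section times the first message against the consent form.
- **Parents know their arm when they decide on consent or fill in baseline.** The trial is unblinded, but when parents are told is not stated.
- **The nonbirthing partner is first contacted after allocation.** This is not so: interest may be assessed earlier, partners may screen separately, and nonbirthing parents can enrol in their own right. What follows allocation for a linked partner is consent and baseline.
- **Power is below 80%.** Sample Size does not say at what point the 166 is counted or which losses the 15% covers. If the 166 means completed baselines, or the 15% already includes these losses, power is not reduced.
- **The result will favour the intervention.** Neither the existence nor the direction of bias follows from the text.

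These limits stand and narrow the point. They do not remove it: the order of steps, the withdrawal rule, the halt to data collection and the intention-to-treat statement are all explicit and cannot all hold. An unseen analysis plan could rename the analysis set but could not recover outcomes that were never collected.

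**Conclusion.** The point holds in this form. As written, the plan produces an analysis set selected after allocation in an unblinded trial, which contradicts its intention-to-treat statement, and it uses as pretest covariate a score measured after randomisation. Linked nonbirthing partners, part of the primary population, are directly exposed.

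The size of the bias is unknown. It is zero if the share and kind of parent excluded are alike in both arms; the non-zero cases in the working run from about 5% to 21% of the 4-point target (0.21/4 to 0.85/4), in either direction, and rest wholly on assumed exclusion rates and prognosis. The power figures hold only on the stated reading of the 166 and the 15%, and on an SD back-solved from the plan's own sample size.

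The point should be settled now. On 15 September 2025 only 16 parents (11 birthing, 5 nonbirthing) had been enrolled, so nearly all of the sample can still be protected.

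**What to change.** **Parents not yet randomised**

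- Re-sequence the automated flow: eligibility, consent, baseline survey, random split, then allocation notice and messages.
- In linked dyads, ask for the partner's consent and baseline before the split where possible, within a short prespecified window. A hold to day 7 would be costly: at two messages a day from the second evening, about five days' wait forgoes roughly 5 × 2 = 10 of the 59 messages, because late enrollees do not receive earlier ones.
- Count the 166 at the split.

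**All consented, randomised parents**

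- Delete the rule in Eligibility Criteria that stops data collection after an incomplete baseline. Continue the 6-week and 6-month surveys and analyse parents as randomised.
- Bring Ethical Considerations, Eligibility Criteria, Screening and Baseline, Intervention Group and Data Analysis into line with one another.

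**Parents already randomised under the present order**

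- Report the numbers randomised, consented and baseline-complete by arm.
- Add a sensitivity analysis that does not adjust for the post-randomisation baseline score.

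If the present order is kept, do not call the analysis intention-to-treat.

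**Cost.** The survey and messaging steps must be re-linked and an ethics amendment obtained. Some parents will start later and miss some early messages, and some will drop out before randomisation rather than after it.

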### Ethical Considerations

This study has been approved by the IWK Health Research Ethics Board (1031429) and is registered with ClinicalTrials.gov (NCT06996067). The CONSORT-EHEALTH (Consolidated Standards of Reporting Trials of Electronic and Mobile Health Applications and Online Telehealth) checklist [26] will be followed to enhance reporting quality for this eHealth intervention trial.

All participants will be asked to provide consent via REDCap (Research Electronic Data Capture; Vanderbilt University) [33], a secure web application for building and managing web-based surveys and databases, followed immediately by the baseline survey. Participants who do not complete the consent form or baseline survey will be considered to have withdrawn from the study.

To maintain confidentiality, all study data will be identified using a study number unique to each participant. Contact information will be collected via TextIt (Nyaruka) [34], a platform used to create and manage 2-way mobile messaging applications, which will be kept separate from survey data collected via REDCap to protect confidentiality.

To encourage survey completion, participants will be offered an honorarium for their time. Electronic gift cards worth CAD $5 (US $3.62) will be provided for each completed survey at baseline, 6 weeks post partum, and 6 months post partum. Participants who complete all 3 surveys will be entered into a draw for an electronic gift card worth CAD $250 (US $181.10). Four separate draws will be held: one each for the birthing parents in the control and intervention groups and one each for the nonbirthing parents in the control and intervention groups.

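### Parents are randomised before consent and baseline, and non-completers are dropped without outcome data, so the stated intention-to-treat analysis is at best a modified one

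*Protocol article*

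**What the plan says.** Four parts of the protocol article bear on this.

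- **Order of steps.** Screening and Baseline states: "Participants will then be randomly assigned to the intervention or control group and asked to complete the consent form and baseline survey". In a participating dyad, "the nonbirthing partner will be sent an SMS text message after randomization", and only then is that partner asked for consent and baseline data. Nonbirthing parents are the population of the primary objective.
- **Non-completers.** Ethical Considerations: "Participants who do not complete the consent form or baseline survey will be considered to have withdrawn from the study". Eligibility Criteria repeats the rule for an incomplete baseline ("Participants who do not fully complete the baseline survey will be considered withdrawn from the study") and adds, for those allocated to the intervention, that "they will continue to receive the messages, but no further data will be collected from them".
- **Open allocation.** Blinding: "participants cannot be blinded and will be informed of their group allocation".
- **Analysis.** Data Analysis: "Data will be analyzed on an intention-to-treat basis", using analysis of covariance adjusted for the pretest score.

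No section places consent or baseline before the split, provides for outcomes from the withdrawn parents, or defines a modified intention-to-treat set.

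**The concern.** Randomisation makes the arms comparable at the moment of allocation. Here two further hurdles, consent and a complete baseline survey, stand between allocation and membership of the analysed set. Those who fail either hurdle leave with no outcome. If the chance of clearing them depends on the arm and also on how the parent will later score, the groups compared at 6 weeks are no longer the groups that were randomised.

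A statistical analysis plan cannot repair this. The loss comes from the order of steps and from a data-collection rule, so the outcomes will not exist when the analysis is run. For linked nonbirthing parents, consent is sought only once the household's arm is fixed, so the issue reaches the primary comparison.

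**Working it through.** **1. The order, checked across sections.** Screening and Baseline puts the split before consent and baseline, both for parents generally and for the dyad partner. Eligibility Criteria confirms it independently: its rule for an unfinished baseline provides for a parent already allocated to the intervention, which presupposes that allocation has happened.

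**2. What can be analysed.** A parent who is randomised but does not finish has no 6-week or 6-month score, lacks a full pretest for the covariance model, and may not have consented to any use of data. The largest analysable set is randomised, then consented, then baseline complete.

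**3. The plan's own figures.** Sample Size gives 141 analysable parents and 15% attrition: 141 / 0.85 = 165.9, rounded up to 166. This reproduces. The SD is not printed. Solving for it from 141 parents, a 4-point difference, 80% power and two-sided 0.05 gives 4 / (1.96 + 0.842) × √(70.5 / 2) = 8.48 with the normal formula, or 8.42 with the t-test. I use 8.42.

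**4. Possible size of the bias.** The protocol gives no completion rates, so everything in this step is assumed:

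- completion p_I (intervention) and p_C (control)
- a latent normal propensity to complete, correlated ρ = 0.3 or 0.5 with the 6-week score, and with the pretest only through that score
- pretest-outcome correlation r = 0.5
- 83 randomised per arm, 10% later random loss, and no true effect

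The mean propensity among completers is m(p) = φ(z) / p, where z is the normal quantile with upper tail p. This gives m(0.95) = 0.109, m(0.90) = 0.195, m(0.85) = 0.274, m(0.75) = 0.424 and m(0.70) = 0.497.

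Approximate bias after pretest adjustment = (1 − r²) × ρ × SD × [m(p_I) − m(p_C)].

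SE = SD × √(1 − r²) × √(1/n_I + 1/n_C).

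Example, 95% vs 85% with ρ = 0.3:
- bias = 0.75 × 0.3 × 8.42 × (0.109 − 0.274) = −0.31
- n_I = 83 × 0.95 × 0.9 = 71.0 and n_C = 83 × 0.85 × 0.9 = 63.5
- SE = 8.42 × 0.866 × √(1/71.0 + 1/63.5) = 1.26
- two-sided type I error = 5.7%

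| Completion, intervention / control | ρ | Bias (points) | Type I error |
|---|---|---|---|
| 95 / 95 | 0.3 or 0.5 | 0 | 5.0% |
| 90 / 85 | 0.3 | −0.15 | about 5% |
| 90 / 85 | 0.5 | −0.25 | about 5% |
| 95 / 85 | 0.3 | −0.31 | 5.7% |
| 95 / 85 | 0.5 | −0.52 | 7.0% |
| 95 / 75 | 0.3 | −0.60 | 7.4% |
| 95 / 75 | 0.5 | −1.00 | 11.9% |
| 90 / 70 | 0.3 | −0.57 | 7.1% |
| 90 / 70 | 0.5 | −0.95 | 10.9% |

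Simulation of the three wider gaps (4000 runs each) gave absolute biases of 0.30 to 0.99 points and type I error of 5.9 to 12.5%, in line with the formula. The minus sign means bias against the intervention. It arises because coping parents are assumed likelier to finish and control is assumed to lose more. Reversing either assumption reverses the sign.

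**5. When the bias vanishes.** With equal completion it is zero even though completers are a selected group. If completion depends on outcome only through the measured pretest, the adjusted bias in simulation is between −0.03 and 0.02 points, with type I error about 5%.

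**The case against.** The strongest reply is that none of this shows a biased trial. The protocol says parents will be told their group but not when, so completion may turn out equal by arm. If struggling parents drop out because of how they are coping at baseline, pretest adjustment largely deals with it. The completion gaps above have no source. All of that stands, and it limits the point to a certain exclusion with a possible bias of unknown size and sign.

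Some stronger readings are tempting, but the document does not support them.

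- **Loss of power.** One might take a further 10% loss at baseline, so that 166 × 0.90 × 0.85 = 127 remain, and read off 76% from an unadjusted t-test. The planned analysis adjusts for the pretest. At r = 0.5 it has about 87% power with 127 parents, so no shortfall follows from these inputs.
- **Non-completers use up the 166.** The sentence saying that parents "will only be considered enrolled and assigned a study number once they text" in after the birth concerns prenatal pre-enrolment only. Sample Size does not say whether 166 is counted at randomisation or at completed baseline, or whether the 15% includes baseline non-completers.
- **Unequal incentives.** Honoraria and draws are offered in both arms, and nothing says parents are told that messages continue without a baseline survey.
- **A contradiction over messages after withdrawal.** Program Content and Design describes a parent who opts out by text. Eligibility Criteria describes an administrative status. Different triggers can have different consequences.

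It is also fair to say that waiting for baseline has a price, since late enrollers miss early messages and partners may pass the 7-day limit. That bears on how the fix is applied, not on whether the present order matches the analysis label.

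**Conclusion.** The point holds in this form: the split precedes consent and baseline, non-completers are excluded with no outcome, and the result is not an intention-to-treat analysis of those randomised. That rests on the text alone and needs no assumption.

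The consequence is less certain. With open allocation, completion may differ by arm. Under assumed gaps of 10 to 20 percentage points and a link to outcome beyond the pretest, the spurious difference is about 0.3 to 1.0 points (8 to 25% of the planned 4), with type I error about 6 to 12%. At a 5-point gap it is at most about 0.25 points, and under equal completion or selection only through the pretest it is about zero. A reader might infer that randomisation has already failed to protect the primary comparison. The document does not support that. It shows an avoidable exposure whose size cannot be known in advance and whose lost data cannot be recovered afterwards.

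**What to change.** - **Reorder.** Move the TextIt split to after consent and baseline are submitted in REDCap. For linked dyads, hold the single household split until both parents have consented and completed baseline where this can be obtained within the enrolment window. Examine partners who consent after the split in a sensitivity analysis.
- **Count from there.** Define the 166 per parent type from that point. The target stays at 141 / 0.85 = 166, and the 15% then covers follow-up loss only.
- **Follow up regardless.** In any case, remove the rule ending data collection for parents who consented. Send them the 6-week and 6-month surveys, analyse them as randomised, and impute a missing pretest. Parents who never consented cannot be recovered this way, which is why the reordering matters most.
- **Parents already randomised.** Report by arm and by role the numbers randomised, consented and completing baseline. Label any analysis that leaves some out as modified intention-to-treat.

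The cost is an ethics amendment and a reconfigured message flow. Allocation comes slightly later, some early messages may be missed, and some partners may pass day 7. The article reports 11 birthing and 5 nonbirthing parents, 16 in all, as of September 15, 2025, so at that date a change would still have covered nearly the whole trial.
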